## Abstract

**Background:**

Depression is seriously affecting the physical and mental health of young people worldwide. Subthreshold depression, as an early stage of depression, is essential for early prevention and treatment of depression. Tai Chi, as a traditional Chinese mind-body therapy, may become an alternative intervention. However, the neurophysiological mechanism of Tai Chi for young people with subthreshold depression remains unclear, restricting its further promotion and application. Therefore, rigorous randomized clinical trials are needed to further observe the intervention effect of Tai Chi on young adults with subthreshold depression and explore the neurophysiological mechanism.

**Method/design:**

This report describes a two-arm, randomized, parallel controlled trial with allocation concealment and assessor blinding. A total of 64 eligible participants are randomly allocated to the Tai Chi group and the waiting list group in a 1:1 ratio. Participants in the Tai Chi group receive 12 weeks of Tai Chi training, with a total of 36 times and each for 60 min. Specifically, the participants in the waiting list group are requested to maintain their routine lifestyle. In this study, the primary outcome measure is the mean change in scores on the PHQ-9 and HAMD-17 between baseline and 12 weeks; the secondary outcomes are the mean change in the scores on CES-D, CPSS, GAD-7, and PSQI. Besides, the saliva cortisol levels and *f*MRI are monitored to explore the mechanism of action of Tai Chi on subthreshold depression.

**Discussion:**

The protocol uses a randomized controlled trial to examine the effectiveness of Tai Chi for young adults with subthreshold depression and explore neurophysiological mechanisms. If the test results are positive, it can be verified that Tai Chi can promote the physical and mental health of young adults with subthreshold depression.

**Trial registration:**

Chinese Clinical Trial Registry ChiCTR1900028289. Registered on 17 December 2019

## Background

Major depressive disorder (MDD) is already a major burden of disease worldwide and is the second most psychiatric disease in the world that causes disability [1, 2]. Subthreshold depression, a pre-stage of MDD [3, 4], has been considered to be an important period of early intervention of MDD. Subthreshold depression is defined as a symptom of depression that not meets diagnostic criteria but also reduces the quality of life and function [5, 6]. It is the leading cause of disability in youth [7, 8], related to stress [9], anxiety [5], insomnia [10], drug abuse [11], social dysfunction [12], and even leads to suicide [13]. Although there are many antidepressant drugs for treating depression, there are still many problems such as drug resistance and side effects. More and more researchers have paid attention to non-drug treatments of subthreshold depression such as mind-body therapy and complementary and alternative medicine.

Tai Chi is a kind of mind-body aerobic exercise, which has been verified to benefit for depressive symptoms [14] and related symptoms such as stress [15] and insomnia [16]. It contains a series of psychologically beneficial components such as meditation, breathing regulation, mental control, and physical exercise [17]. Many studies have applied Tai Chi alone or in combination with the treatment of depression. For example, Lavertsky et al. [18] combined antidepressant with Tai Chi to jointly intervene in elderly depressed patients with partial response to escitalopram. They revealed that patients who received Tai Chi training had better improvement in depression level, and the quality of life and cognition; besides, the benefits of Tai Chi as adjunctive intervention far exceed standard antidepressant treatment or adjuvant medication. Some researchers even use it alone to treat MDD. Yeung et al. [19] used a small sample of randomized controlled trials to demonstrate that Tai Chi is feasible and safe in the treatment of Chinese American depression patients, observing an improvement in the treatment response rate and remission rate in the Tai Chi intervention group. Further research proves that Chinese Americans with major depressive disorder underwent a 12-week Tai Chi training. Compared with the health education group and the waiting list group, the response rate and remission rate of the Tai Chi group both exceeded 50%, indicating that Tai Chi can effectively reduce the anxiety and depressive symptoms of depressive patients and can be used as an adjuvant treatment for patients with depression. Chou et al. [20] explored the effect of Tai Chi’s social support on Chinese elderly patients with major depression. The results illustrated that Tai Chi had a significant effect on depressive symptoms when controlling age, gender, and education. The intervention effect is not significant when social support was controlled. Therefore, it is speculated that social support may be part of the reason for Tai Chi treatment of depression symptoms. The practice of Tai Chi was essentially a social activity.

A recent study used mindfulness combined with simplified 24 short-form Tai Chi Chuan to treat subthreshold depression in adolescence [21]. In this study, Zhang et al. [22] demonstrated that the depression level of adolescents with subthreshold depression can be improved by 8-week mindfulness-based modified Tai Chi Chuan. However, it is not clear whether mindfulness or tai chi are an effective part of intervention for subthreshold depression.

Among the many physiological factors leading to subthreshold depression, dysfunction of the hypothalamic-pituitary-adrenal (HPA) axis is considered to be an important cause [23]. Some studies have discovered that patients with subthreshold depression have dysfunction of HPA axis [24]. The HPA axis is part of the neuroendocrine system that controls the body’s stress response and regulates mental and emotional activities, such as stress and depression. There is evidence that the activity of the glucocorticoid receptor (GR) is decreased when the body is depressed, causing a decrease in the negative feedback inhibition of the HPA axis and excessive activation of the HPA axis [25]. GR can penetrate the blood-brain barrier and bind to the GR receptors in the brain, influencing the structure and function of the brain [26]. Research has indicated that hippocampus, prefrontal cortex, and amygdala are the most abundant brain regions of GR receptors [27] and directly related to emotional problems such as depression and psychological stress [28]. Some studies have revealed that mild depression or subthreshold depression were associated with a decrease in gray matter volume in the frontal cortex, anterior cingulate gyrus, thalamus, supraorbital/temporal lobe, and suprafrontal gyrus [29–31]. Li et al. discovered that compared with the healthy control group, the gray matter volume of the bilateral globus pallidus and the central anterior gyrus decreased in the patients with subthreshold depression, and the gray matter volume of the left thalamus and the right anterior cingulate cortex/medial prefrontal cortex increased [32].

Previous studies have illustrated that Tai Chi training has a regulatory effect on the function of the HPA axis and depression-related brain regions [33–35]. Nedeljkovic et al. [36] investigated that a 12-week, twice-weekly, 60-min Tai Chi practice can significantly improve the stress and negative emotions of the practitioner compared to the waiting list and further reduce the HPA axis response to stress and the concentration of salivary cortisol. Tao et al. [37] concluded that 12-week Tai Chi practice increased the gray matter volume of the medial temporal lobe, putamen, and insula. After a 12-week Tai Chi practice, a significant decrease in resting-state functional connections exhibited between the dorsolateral prefrontal cortex and the left superior frontal gyrus and anterior cingulate cortex [38].

Above all, this study uses a randomized controlled trial design to observe the effects of 12-week traditional Tai Chi on young adults with subthreshold depression from the perspective of depression-related symptom, HPA axis functions, and neuroimaging. This research provides evidence-based medical for the further application of Tai Chi in subthreshold depression.

## Methods/design

### Study design

The effectiveness of traditional Tai Chi training on young adults with subthreshold depression is assessed in a randomized, single-blind, and parallel-controlled trial. Outcome assessors and data analysts will be blinded. A total of 64 eligible participants are randomly allocated to the Tai Chi group and the waiting list group in a 1:1 ratio. Participants in the Tai Chi group receive 12 weeks of Tai Chi training, with three times a week, each for 60 min, a total of 36 times. The participants in the waiting list group are requested to maintain their routine lifestyle. Primary and secondary outcomes are measured at baseline, 12 weeks after the intervention, and after an additional 12-week follow-up period. Primary and secondary outcomes are measured at baseline, 12 weeks (at the end of intervention), and 24 weeks (after 12-week follow-up period). A flow diagram of the study design is illustrated in Fig. 1, and the time points for the study visits are presented in Fig. 2.

**Fig. 1 Fig1:**
[figure not shown]
Flow diagram of participants. Abbreviations: PHQ-9, The 9-item Patient Health Questionnaire; HAMD-17, The 17-item Hamilton Depression Scale; CES-D, Center for Epidemiological Studies Depression Scale; CPSS, Chinese Perceived Stress Scale; GAD-7, A 7-item Generalized Anxiety Disorder; PSQI, Pittsburgh Sleep Quality Index; fMRI, functional magnetic resonance imaging

**Fig. 2 Fig2:**
[figure not shown]
SPIRIT figure. Schedule Of enrolment, interventions, and assessments

### Sample size estimation

In this study, the influence of Tai Chi on the depressive symptom of young adults with subthreshold depression was observed. When estimating the sample size, PHQ-9 and HAMD-17 were used as the main effect indicators to calculate the required sample size. Besides, the larger sample size was used as the sample size of this study.

The sample size estimation was based on the improvement in PHQ-9 (The 9-item Patient Health Questionnaire) scores. According to relevant published literature [22], the mean and its SD of PHQ-9 scores after the 8 weeks of mindfulness-based Tai Chi training for subthreshold depression adolescents were 6.03 and 2.18 points, respectively, while the mean and its SD of PHQ-9 scores in the control group were 8.10 and 2.52 points, respectively. According to the above results, a sample size of 58 participants was calculated to sufficiently detect the target effect size (0.879) with a type 1 error of 5% (*α* = 0.05) and 90% power (*β* = 0.10) by Gpower V.3.1.9.2 software. Assuming a dropout rate of 10%, a total of 64 participants are necessary, with 32 participants in each group.

Simultaneously, according to the research [21], the total score of HAMD-17 obtained by regular Tai Chi training to improve patients with major depressive disorders was 9 ± 5 points while the HAMD-17 score of control group patients with major depressive disorders was 15 ± 7 points. Based on the above results, a sample size of 46 participants was calculated to sufficiently detect the target effect size (0.986) with a type 1 error of 5% (*α* = 0.05) and 90% power (*β* = 0.10) by Gpower V.3.1.9.2 software. Assuming a dropout rate of 10%, a total of 52 participants are necessary, with 26 participants in each group.

Since the sample size calculated using PHQ-9 as the result indicator is more than HAMD-17, this study chose PHQ-9 as a basis to estimate the sample size of this study, and a total of 64 subjects were recruited.

### Participants and recruitment

A total of 64 participants were recruited at various communities in Fuzhou, China. Participants will be recruited by distributing leaflets, posters, recruitment information on WeChat, or other online platforms. Besides, a recruiting station in places where young adults are concentrated was set up, such as universities and business districts. Interested volunteers can contact the research assistants, who would screen applicants according to the inclusion criteria and exclusion criteria. The research assistant introduced the entire study and informed consent to the volunteers in detail, mainly including the research cycle and intervention methods. Meanwhile, the research assistant explains the grouping situation. Participants should obey random allocation and follow the prescribed scheme of each group (such as the participants had to agree not to participate in Tai Chi if they were randomized to the waiting list group); otherwise, they are excluded. Eligible volunteers are invited to join the study, sign informed consent, and then be scheduled for baseline assessment.

### Inclusion criteria

In order to be eligible for the study, participants must meet the following criteria needed:
Centre for Epidemiological Studies Depression Scale [CES-D] score ≥ 16, reaching the experience subthreshold depression [39].The Mini International Neuropsychiatric Interview (MINI version 5.0) was used to determine that major depression was not achieved and there was no significant risk of suicide according to Diagnostic and Statistical Manual of Mental Disorders (Fifth Edition) (DSM-V) criteria.Aged between 18 and 45 years.No treatment related to depression has been received in the past 6 months.Regularity mind-body exercises (Tai Chi, Baduanjin, Yoga, meditation, etc.) were not performed within half a year (regularity mind-body exercise refers to exercise at least twice a week, at least 20 min each time).No contraindication of MR examination.Written informed consent.

### Exclusion criteria

Exclusion criteria for participants were:
Meeting DSM-V criteria for a major depressive episode, bipolar disorder, or psychotic disorder.Have a history of MDD in the past 6 months.Recent bereavement.In the use of glucocorticoid drugs, psychotropic substances or addiction disorders, such as drug dependence and alcohol abuse.Suffering from endocrine and metabolic diseases (Cushing’s syndrome, Addison’s disease, etc.)Have a history of head trauma or a history of serious diseases such as heart, liver, and kidney.Pregnant women and lactating women.Participate in other clinical trials that will affect the results of this study.

### Withdrawal or dropout criteria

Participants will withdraw from this trial according to the following:
Participants who decide to withdraw.Development of serious diseases hinders the continuation of the trial.Suffering from a serious adverse event (AE) related to the Tai Chi training.Participations in the waiting list group have regularly engaged in Tai Chi exercise.

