### Statistical analyses

Analysis of all data in this trial was performed by an independent statistician who is not involved in the evaluation of the results using the SPSS V.24.0 software package, with a statistical significance of a two-sided *p* value less than 0.05. Normally distributed continuous variables were described as mean ± standard deviation (SD), and non-normal variables were described as the median and interquartile range (IQR). Categorical variables were reported as frequencies or percentages. In this study, basic data including age, gender, BMI [49], education level [50], family factors [51], economic ability [52], and screen time [7] were collected, and basic data were proposed as covariates in this study. Analysis of the primary and secondary outcomes was performed based on the intention-to-treat (ITT) population and per-protocol (PP) population. The result of the ITT analysis was compared with that of the PP analysis to determine whether the results are consistent. Multiple imputations were used to impute missing data. ITT analysis was performed on all subjects in the Tai Chi group and waiting list group. In this study, after the subjects were randomly divided into groups, regardless of whether they received the treatment of the group, they were eventually included in the assigned group for statistical analysis, even though they withdrew from the trial due to adverse reactions. Differences between groups in the Tai Chi group and the waiting list group at each time point (12 weeks after intervention or 12 weeks’ follow-up) were analyzed using Student’s *t* test or Mann-Whitney *U* test. The interaction effect of group × time was analyzed by the linear mixed model with restricted maximum likelihood. Pearson correlation or Spearman correlation was adopted for correlation analysis.

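### Withdrawing waiting-list participants who take up Tai Chi is a one-arm, adherence-based rule that can create outcome-related missing data and undermine the intention-to-treat analysis

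*Protocol article*

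**What the plan says.** Four parts of the protocol article bear on this.

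- **Withdrawal or dropout criteria.** The list opens with "Participants will withdraw from this trial according to the following". Its last item is "Participations in the waiting list group have regularly engaged in Tai Chi exercise". Another item, "Suffering from a serious adverse event (AE) related to the Tai Chi training", will in practice arise only in the Tai Chi arm, but it concerns safety. No item covers a Tai Chi participant who stops attending or never practises.
- **Data collection and management.** A participant who withdraws is asked about continuing with data collection. Follow-up data are pursued if the answer is yes.
- **Statistical analyses.** "ITT analysis was performed on all subjects in the Tai Chi group and waiting list group". Of randomised subjects the section says that, "regardless of whether they received the treatment of the group, they were eventually included in the assigned group for statistical analysis". The only reason for withdrawal that it names is adverse reactions. A PP analysis is planned alongside and compared with ITT, and missing data are multiply imputed. The imputation model is not described.
- **Participants and recruitment.** Volunteers must accept random allocation and their group's scheme; "otherwise, they are excluded".

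**The concern.** A control participant who takes up Tai Chi has departed from the assigned condition. ITT exists to keep such a person measured and counted as randomised. The withdrawal list instead ends that person's participation, although the participant has not asked to leave and safety is not at issue.

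The visits at 12 and 24 weeks, which were scheduled for everyone, then depend on a new expression of willingness. This happens in one arm only, and the trigger may be related to outcome: the trial's own hypothesis is that Tai Chi lowers depression scores, and people who seek it out may also differ in symptoms or motivation. If those outcomes are not obtained, the observed control data come mainly from people who did not practise Tai Chi, and the ITT result leans on imputation for the rest. An analysis plan cannot recover assessments that never took place, so the matter belongs in the protocol.

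**Working it through.** **1. The plan's own figure (Sample size estimation).** PHQ-9 means are 6.03 (SD 2.18) with Tai Chi and 8.10 (SD 2.52) in controls.

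- Difference: 8.10 − 6.03 = 2.07.
- Pooled SD: √[(2.18² + 2.52²)/2] = 2.356.
- Effect size: 2.07/2.356 = 0.879, as stated.
- A two-sided two-sample t test at 5% with 90% power needs 28.19, so 29 per arm, or 58 in total, as stated.
- Adding 10%: 58 × 1.10 = 63.8, so 64, or 32 per arm, as stated.

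**2. What the rule does to one participant.** Reading the sections in sequence:

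- A control starts regular Tai Chi and is withdrawn from the trial (withdrawal criteria).
- Later outcomes are sought if the person is willing (data management).
- The person stays in the control group for ITT, with observed or imputed values (statistical analyses).

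The person is not lost from the analysis set. The person's measured outcome may be.

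**3. Illustration of the size.** Let *k* of 32 controls cross over. Let their week-12 PHQ-9 differ by *δ* from that of the *other* controls, whose mean is *m*; take it as lower by *δ*.

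- Mean of the control arm as randomised: [(32 − *k*)·*m* + *k*·(*m* − *δ*)]/32 = *m* − *kδ*/32.
- Mean if no crossover outcome is recovered and imputed values resemble the other controls: *m*.
- Shift: *kδ*/32.

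The divisor is 32 because *δ* is measured from the other controls; 32 − *k* would apply only if *δ* were measured from the mean of the whole arm. With *δ* = 2.07:

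| *k* | Shift (points) | Share of 2.07 |
|---|---|---|
| 3 | 3 × 2.07/32 = 0.19 | 3/32 = 9% |
| 5 | 5 × 2.07/32 = 0.32 | 5/32 = 16% |

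If crossovers score lower, the control mean is too high and the comparison favours Tai Chi. If they score higher, the direction reverses.

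**4. The other side of the trade.** If the same crossovers are measured and kept as assigned, with full loss of contrast, the SD unchanged and all 32 per arm evaluated, the effect size becomes 0.879 × (32 − *k*)/32.

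| *k* | Effect size if kept | Power if kept | Power if removed |
|---|---|---|---|
| 0 | 0.879 | 93.3% | – |
| 3 | 0.797 | 88.0% | 92.1% (32 v 29) |
| 5 | 0.742 | 83.2% | 91.1% (32 v 27) |

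The removed column keeps the effect size at 0.879, a contrast that is no longer ITT. Losing these participants therefore costs little power. The problem is what the estimate then represents.

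**The case against.** A reader might infer that the rule is a post-randomisation exclusion that contradicts the stated ITT analysis. The documents do not support that. Withdrawal from the trial is not removal from the analysis set, and the statistical section keeps every randomised subject in the assigned group, including people of whom it says "they were eventually included in the assigned group for statistical analysis, even though they withdrew from the trial due to adverse reactions". A separate PP analysis is declared, so ITT is not a per-protocol analysis under another name.

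Nor does the recruitment text add a second exclusion. The clause "the participants had to agree not to participate in Tai Chi if they were randomized to the waiting list group); otherwise, they are excluded" describes what volunteers must agree to, and the next sentence moves to consent and baseline assessment. It reads as a condition of entry.

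Other points on that side also stand. Follow-up after withdrawal is provided for, and making it depend on willingness is proper. The imputation model may sit in an analysis plan that is not shown, so one cannot say that it ignores Tai Chi exposure. Nothing in the protocol indicates how many controls would cross over, and several features make it less likely: the prior agreement, the entry requirement of no recent regular mind-body exercise, and the option of Tai Chi after 24 weeks.

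These points narrow the concern without removing it. The follow-up provision only softens a withdrawal that the protocol need not impose, and the safety criterion on the Tai Chi side is no counterpart to a rule about adherence.

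**Conclusion.** The point holds as a conduct rule that sits badly with ITT and can produce outcome-related missing data in the control arm. It does not hold as a contradiction of the ITT definition.

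The illustrative shift in the control mean is 0.19 PHQ-9 points for 3 crossovers and 0.32 points for 5. Both are upper bounds for their scenario. They assume those counts, a 2.07-point difference from the other controls, no outcomes recovered, and imputed values like those of the other controls. Each outcome actually collected, or an imputation model that reflects Tai Chi exposure, would reduce them. The direction is not fixed by the documents.

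**What to change.** In the withdrawal criteria, delete regular Tai Chi practice by a waiting-list participant as a reason to leave the trial. State instead that:

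- such practice is recorded as a protocol deviation, using the activity logs already required of all participants;
- the scheduled 12- and 24-week assessments go ahead as for everyone else;
- the participant is analysed as randomised in ITT;
- the practice affects membership of the PP set only.

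The cost is a short amendment; no new visits or instruments are needed. The statistical price is that crossover may dilute the ITT estimate. In the illustration the 2.07-point difference would become 2.07 − 0.19 = 1.88 with 3 crossovers or 2.07 − 0.32 = 1.75 with 5, if those participants lost all contrast with the Tai Chi arm. The dilution should be slight if crossover is rare, and the planned comparison of ITT with PP would help to show its effect.
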